**Secondary endpoints**

The secondary objectives of this study are to evaluate:

- the duration of postoperative drainage
- the daily drainage volume
- the total drainage volume
- the number of repeated lymphocele aspirations and the volume.
- the total volume of lymph aspirated
- the incidence of postoperative febrile episodes
- the length of the hospital stay
- the length of time to onset of adjuvant chemotherapy

**3.5.4 Evaluation of medicinal dosages and of pharmacokinetic**

A pharmacokinetic study will be realized with a sample before injection at V1 (injection day) and a sample at V4 (J19-23 post-injection). If the V4 visit corresponds to more than 24 days after injection, this visit will be advanced in order to respect samples times. An electrocardiogram (ECG) will be done at the same time that sampling for pharmacokinetic.

# 6. Statistical methods

## 6.1. Statistical methods to be used

We recommend a prospective, randomized, two-center trial according to a Bayesian design with a control arm receiving a placebo.

## 6.2. Efficacy evaluation:

The evaluation criterion will be the proportion of patients who did not have symptomatic, postoperative axillary lymphoceles defined as the absence of aspiration or a unique or iterative aspirations global volume of lymphoceles inferior to 60cc inclusive (≤) in the 28 days after the intervention or a systematic aspiration volume at the 28th day inferior to 120cc inclusive (≤).

## 6.3. Safety assessment

Safety will be evaluated during each visit and recorded in the CRFs.

## 6.4. Number of subjects

A total of 90 patients will be included over 12 months with 45 patients in the treatment group and 45 patients in the treatment-free group. In principle, there is no need to justify the number of subjects in a Bayesian study (15). However, the concept of desired accuracy of the success rate can be used based on its distribution a posteriori to define a test sample to be included.

## 6.5. Primary endpoint analysis

The statistical analysis will be carried out sequentially after observing the principal criterion (i.e. success is defined as a total volume of lymphoceles following single or repeated aspiration ≤ 60 cc in the 28 days following surgery or a routine aspiration volume on the 28th day ≤ 120cc) of each patient included for each randomization group, with or without treatment.

It involves estimating the probability of a response in each group (proportion of patients who will not have undergone lymphocele aspiration or the aspiration of a total volume of ≤ 60cc or ≤ 120cc for the aspiration carried out on the 28th day after surgery) using a Bayesian design based on a beta-binomial model (16,17). With the Bayesian approach, the response rate in each group (*i*) is considered as a random variable *primarily* of density focused on the anticipated response rate of 80% in the group receiving treatment and 60% in the treatment-free group, which will be sequentially updated as the observations are made according to a so-called *a posteriori* law.

*A priori* density will be selected for each group from the Beta conjugated laws group, defined by its two parameters *ai*and *bi* (with a life expectancy = and variance = , with *i=1,2* according to the group considered). The Bayesian estimator of the response rate in each group will be expectancy of the *a posteriori* law, i.e. the Beta law of parameters *Ani* and *Bni* , defined on the basis of those of the *a priori* law and the number *ni* of inclusions, as shown below. *Ani=a+ri* and *Bni=b+ni-ri,* where *ri* represents the number of responses observed on the *ni* included in the *i* group. The following estimator is, therefore, obtained: .

## 6. 6. Rules for discontinuation

Bayesian rules for discontinuation will be calculated sequentially in order to possibly make a decision to stop inclusions in eac group based on the four following criteria (17, 18):

- - The first two discontinuation criteria are defined on the basis of the *a posteriori* law of **: (i) ***criterion 1*** = *a posteriori* probability that the response rate **is less than 60% (considered as the maximum inefficacy threshold) and (ii) ***criterion 2*** = *a posteriori* probability that the response rate **is greater than 80% (considered as the minimum efficacy threshold) will be calculated*.*
  - The third discontinuation criterion will be based on the predictive distribution of responses (*s*) out of *zi=5* next included , i.e., ***criterion 3*** =
  - The fourth discontinuation criterion will be based on the maximum expected gain in terms of the width of the 95% credibility interval of the response rate out of z = 5 next included: ***criterion 4*** = , whereis the 95% credibility interval (= 0.05) of , calculated after inclusion of *ji* subjects, such that .

The discontinuation decisions are as follows:

- - - - *If criterion 1 > 0.90: discontinuation of inclusions with conclusion of inefficacy*
      - *If criterion 2 > 0.90, discontinuation of inclusions with conclusion of efficacy*
      - *If criterion 3 > 0.90: discontinuation of inclusions with conclusion of efficacy*
      - *If criterion 4 < 0.05: discontinuation of inclusions with conclusion of efficacy*

An independent committee will meet to confirm the decision to continue or discontinue inclusions in the considered group based on the results of the sequential analysis.

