6.1. Statistical methods to be used [28](#__RefHeading___Toc246224633)

6.2. Efficacy evaluation: [28](#__RefHeading___Toc246224634)

6.3. Safety assessment [28](#__RefHeading___Toc246224635)

6.4. Number of subjects [28](#__RefHeading___Toc246224636)

6.5. Primary endpoint analysis [28](#__RefHeading___Toc246224637)

6. 6. Rules for discontinuation [29](#__RefHeading___Toc246224638)

Summary of Protocol

1. **Background**

The principal morbidity following axillary node dissection within the scope of breast cancer surgery is the post-operative development of lymphocele. According to the literature, incidence can vary from 4 to 89% depending on the type of surgery, whether or not a drain is inserted or a compression dressing applied and the time at which the drain is removed… In our experience, the incidence is 40% [IGR (Gustave Roussy Institute) data focusing on 70 patients between November 2008 and February 2009].

Encouraging results in terms of reducing postoperative lymphoceles as well as drainage duration and volume using Octreotide have been recorded in two recent studies. A new molecule developed by Novartis Laboratories, namely pasireotide, is a somatostatin analog possessing strong affinity for several somatostatin receptors (30 to 40 times greater for sst1 and sst5, 5 times greater for sst3 and equivalent for sst2)

1. **Purpose**

The purpose of this trial is to assess the efficacy of a pre-surgical injection of pasireotide LAR in reducing the postoperative incidence of symptomatic lymphoceles following axillary node dissection.

The secondary objectives are to assess the efficacy of prolonged release pasireotide on the duration of postoperative drainage, the daily drainage volume, the total drainage volume, the number of repeated lymphocele aspirations and the volume, the total volume of lymph aspirated, the incidence of postoperative febrile episodes, the length of hospital stay, and the length of time to onset of adjuvant chemotherapy. It is also to assess the safety of prolonged release pasireotide.

1. **Trial design**

We recommend a prospective, randomized, two-center trial according to a Bayesian design with a control arm receiving a placebo.

1. **Trial population**

All female patients for whom mastectomy - axillary node dissection is indicated at the pre-surgical stage will be eligible for inclusion. Control population of an identical size: randomization 1:1.

1. **Study Procedure**

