# 2- Study objectives

## 2.1 Primary objective

The primary objective of this study is to assess the efficacy of a preoperative prolonged release pasireotide injection in the reduction in the incidence of symptomatic, postoperative axillary lymphoceles following mastectomy-axillary node dissection.

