# 3. Study protocol

## 3.1. Global study design

### 3.1.1. Type of trial

Randomized, multicenter, prospective, Bayesian trial with a control group.

Since the control group receives a placebo injection, it can be used to validate the incidence of lymphocele following mastectomy and axillary node dissection during the study period (the incidence varies considerably according to the literature). It can be used to calculate the study number if a decision is taken to carry out a phase III study.

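### Efficacy is concluded arm by arm against fixed 60% and 80% limits, and each arm can close alone, so the concurrent placebo result never enters the efficacy conclusion of a randomised trial

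*Protocol*

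**What the plan says.** The primary objective (section 2.1) is efficacy "in the reduction in the incidence of symptomatic, postoperative axillary lymphoceles following mastectomy-axillary node dissection". Section 6.1 describes a "prospective, randomized, two-center trial according to a Bayesian design with a control arm receiving a placebo". The Summary of Protocol adds: "Control population of an identical size: randomization 1:1". Section 3.4.3 makes the trial double blind, and section 6.4 plans 45 patients per arm.

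The reason for a control is uncertainty about the background rate. Section 1.2 cites an incidence of 4 to 89% in the literature, against 40% and 39.3% at the two centres. Section 3.2 says that a control group is needed for this reason. Section 3.1.1 adds that "it can be used to validate the incidence of lymphocele following mastectomy and axillary node dissection during the study period", and that the control can help to size a phase III trial.

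Section 6.5, the primary analysis, is arm-wise: "It involves estimating the probability of a response in each group". It uses a beta-binomial model with priors centred at 80% (treatment) and 60% (control), and the estimator is each arm's own posterior mean. The prior weights are not given.

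Section 6.6 is also arm-wise: "Bayesian rules for discontinuation will be calculated sequentially in order to possibly make a decision to stop inclusions in eac group". Criterion 1 is the posterior probability that the arm's rate lies below 60%; above 0.90 it means inefficacy. Criterion 2 is the posterior probability that the rate lies above 80%; above 0.90 it means efficacy. The independent committee confirms the decision for the group under consideration.

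**The concern.** A control arm is included because the historical rate cannot be relied on, yet the efficacy decision uses fixed limits equal to the anticipated rates and does not look at the control. If the success rate in these patients is well above 60% without any drug, the treatment arm can pass criterion 2 and be called effective while placebo does just as well.

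The same rules apply to the placebo arm, which can therefore be stopped for inefficacy, a conclusion with no clear meaning for a control. Once one arm closes, all later patients go to the other. They have no concurrent control, and the blind is at risk. The trial could end as two series of different size and calendar period.

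**Working it through.** **Inputs from the protocol.** 45 per arm (6.4); prior centres 0.80 and 0.60 (6.5); limits 0.60 and 0.80, cut-off 0.90, stopping by group (6.6). The protocol reports no operating characteristics for these rules, so there is no figure of its own to reproduce.

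**Assumptions.** Prior weight k = 1, 2, 5, 10 or 20 patients, that is Beta(0.8k, 0.2k) for treatment and Beta(0.6k, 0.4k) for control. A look after every patient, from patient 10 or from patient 1. Immediate outcomes. Criteria 3 and 4 are left out because their formulas are not legible in the text at hand.

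**Rule.** After r successes in n patients the posterior is Beta(a + r, b + n - r). The arm stops for inefficacy if P(p < 0.60) > 0.90 and for efficacy if P(p > 0.80) > 0.90. Stopping probabilities follow exactly by carrying the binomial probability of each (n, r) forward to n = 45 and removing the paths that have stopped. The two arms are independent.

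**One look at n = 45.** Criterion 2 needs at least 40/45 (89%) for every k above, whatever the control shows. Two cases with k = 2:
- 40/45 in both arms: the treatment posterior is Beta(41.6, 5.4) and P(p > 0.80) = 0.95, so efficacy is concluded. With the same prior in both arms, P(pT > pC) is 0.50 by symmetry.
- 36/45 against 27/45, the anticipated 80% and 60%: the treatment posterior is Beta(37.6, 9.4) and P(p > 0.80) = 0.53, so criterion 2 is not met at that look. With Beta(1,1) in both arms, P(pT > pC) = 0.98.

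**Sequential use.** Percent of trials, first look at patient 10 (in brackets: looks from patient 1).

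| Prior weight k | Pasireotide 'effective', both arms 60% | both 80% | both 90% | Placebo stopped for 'inefficacy' at true 60% | Arms close at least 5 apart, 80% vs 60% |
|---|---|---|---|---|---|
| 1 | 2.2 (22.1) | 39.2 (62.0) | 89.1 (93.7) | 28.1 (40.1) | 51.6 (62.7) |
| 2 | 1.6 (13.4) | 36.6 (53.7) | 88.3 (92.0) | 27.3 (37.6) | 49.5 (61.7) |
| 5 | 1.2 (3.3) | 33.4 (38.6) | 87.1 (88.4) | 25.3 (30.9) | 45.0 (51.5) |
| 10 | 0.8 (1.2) | 28.4 (29.9) | 84.7 (85.1) | 21.3 (23.1) | 39.3 (42.0) |
| 20 | 0.2 (0.2) | 19.5 (19.5) | 79.7 (79.7) | 15.2 (15.4) | 28.8 (29.0) |

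**Comparative rule on the same 45 + 45 patients.** The chance of success is the sum, over all (rT, rC), of Bin(rT; 45, pT) × Bin(rC; 45, pC) where P(pT > pC | data) exceeds the cut-off. No interim looks.
- Beta(1,1) in both arms, cut-off 0.95: false positives 5.3% at 60/60, 4.7% at 80/80, 4.4% at 90/90; power 66% at 80% vs 60%.
- Beta(1,1) in both arms, cut-off 0.90: about 10% false positives; power 80%.
- The protocol's 80% and 60% centres at weight 10, cut-off 0.95: 9-10% false positives, because the priors already favour treatment.

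**The case against.** The strongest defence is that this is a randomised phase II trial with a calibration arm. The objective does not say that the reduction is relative to placebo. Section 3.1.1 gives the control the task of checking the incidence, and section 3.2 treats a phase III as premature. That reading is plausible, and it stands as a possibility. But the protocol never declares the design non-comparative, and even a calibration arm has no effect if efficacy is concluded without consulting it. A SAP might add a contrast. The protocol itself, however, fixes the primary analysis and the conclusions by arm, so this is not detail left open.

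Some stronger inferences are not supported:
- A reader might infer that any departure of the control rate from 60% produces a wrong conclusion. It does not: with both arms at 60% and a first look at patient 10, criterion 2 misfires in 0-2% of trials. The problem comes with large upward departures. The 90% case implies 10% incidence, which lies inside the cited 4-89% but far from the centres' 40%, and the literature range mixes surgical and drainage practices.
- A reader might infer that closing an arm reveals allocation to everyone. The protocol does not say who is told; the randomisation centre informs the injecting nurse. Unblinding is a risk, not a stated consequence.
- A reader might infer that 60% is the wrong rate for this endpoint. The volume definition behind the 40% incidence is not given, so a mismatch is possible but not shown.
- The control is not wholly ignored: section 6.5 estimates its rate. It is absent only from the efficacy conclusion.

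The larger bracketed percentages also depend heavily on looking from the first patient.

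**Conclusion.** The point holds and should be settled before the plan is used. Followed as written, sections 6.5 and 6.6 can declare pasireotide effective when it does no better than placebo: in 80-89% of trials (80-94% with looks from patient 1) if both arms are truly 90%, in 20-39% (20-62%) if both are 80%, and in 0-2% (0-22%) if both are 60%. At a true 60%, placebo is stopped for inefficacy in 15-28% (15-40%). At the anticipated rates the arms close at least 5 patients apart in 29-52% (29-63%), which would end concurrent randomisation.

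These are ranges over assumed prior weights, with criteria 3 and 4 left out, so they are not the properties of the full design. The 28-day outcome lag would soften the imbalance between arms. The structural point, that no between-arm quantity is defined, needs none of these assumptions.

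**What to change.** In section 6.5, rest the primary conclusion on the posterior of pT - pC. Report its mean, its 95% credibility interval and P(pT > pC | data), with a cut-off stated in advance. Use the same weak prior in both arms, for example Beta(1,1), instead of priors centred at 80% and 60%; the 5% and 66% above hold only with such a common prior. Keep the arm-wise posteriors as description.

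In section 6.6, apply every stopping decision to the whole trial and never to one arm. The cut-off and any interim looks are the sponsor's choice; if looks are kept, recalculate the error rate and power for that schedule.

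If a non-comparative phase II with a calibration arm was intended, say so, state how the control result qualifies any efficacy conclusion, and still remove arm-wise closure.

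The cost is a rewording of 6.5 and 6.6 with the same patients and data. The downside is that the modest comparative power for 80% against 60% becomes visible: 66% at a cut-off of 0.95, or 80% at 0.90 with about 10% false positives.

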## 2.2 Secondary objectives

The secondary objectives of this study are:

- to evaluate the efficacy of prolonged release pasireotide on:

- the duration of postoperative drainage
- the daily drainage volume
- the total drainage volume
- the number of repeated lymphocele aspirations and the volume.
- the total volume of lymph aspirated
- the incidence of postoperative febrile episodes
- the length of the hospital stay
- the length of time to onset of adjuvant chemotherapy

- to evaluate the safety of prolonged release pasireotide

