### 3.1.2. Study design

- The Ji data correspond to the length of time compared to the injection of pasireotide or placebo [J1 = day of injection], Ki data correspond to the duration of the procedure [K0=day on which surgery is performed].
- Screening: reporting and presurgical visit
  - Check for compliance with inclusion and non-inclusion criteria
  - Explanation of the trial to the patients
  - Issue of the Patient Information Letter
- Baseline visit (V1 = J1) 7 to10 days before surgery (K-10 to K-7):
  - Consent form signed
  - Injection of pasireotide or placebo by a consultation nurse who will not be present during subsequent visits since aspiration may be required.
  - Recording of adverse events
  - Blood sample for pharmacokinetic monitoring
  - ECG
- Visit V2 (day of surgery or day after surgery [K0 or K1]): collection of data concerning the operation (type of surgery, duration, intraoperative complications, type and number of drains)
  - Recording of adverse events:
- Visit V3 (day of discharge: K4 to K7 post-surgery): Summary of the daily collection of postoperative data:
  - The daily and total drainage volumes
  - Date on which drains were removed and overall duration of drainage
  - Postoperative complications (hematoma, skin necrosis, etc.)
  - Whether aspiration of a symptomatic lymphocele was required
  - Length of hospital stay
  - Recording of adverse events:
- Immediate postoperative visit (V4): 14+/- 2 days following surgery (K12 to K16)
  - The number of repeated lymphocele aspirations and the volume (patients requiring an aspiration will be seen during the interval between two consultations at the hospital and data will be colligated in the medical file. To ensure the lymphoceles sufficiency, a free phone number will be given to the patient in order that she could report any event if necessary.)
  - Recording of adverse events
  - ECG
  - Blood sample for pharmacokinetic monitoring
- Postoperative visit (V5): 28+/- 4 days following surgery (K24 to K32)
  - Routine lymphocele aspiration is considered positive if the volume aspirated exceeds 120cc.
  - The number of repeated lymphocele aspirations and the volume (patients requiring an aspiration will be seen during the interval between two consultations at the hospital and data will be colligated in the medical file.
  - Adjuvant chemotherapy start date, if required
  - Recording of adverse events
- Follow-up visits at two months (V6)
  - Recording of adverse events

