### 3.4.2. Treatment assignment

Patients will be randomized to receive either an injection of prolonged release pasireotide 60 mg or a placebo injection (physiological serum), which will be administered intramuscularly 7 to 10 days before scheduled surgery.

Randomization will be stratified on

1. whether or not a neo-adjuvant treatment has been administered prior to surgery.
2. overweight/obesity with a BMI > 25
3. the including center

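### Section 6.6 sets no minimum number of patients before an efficacy stop, so a short run of early successes can close the pasireotide arm

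*Protocol*

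**What the plan says.** Protocol section 6.5 sets the frequency of analysis: "The statistical analysis will be carried out sequentially after observing the principal criterion" of each patient, separately in each arm. The response rate in the pasireotide arm has a Beta prior, described as a "density focused on the anticipated response rate of 80% in the group receiving treatment". Its two parameters are not given.

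Section 6.6 defines criterion 1 as the posterior probability that the response rate is below 60%, and criterion 2 as the posterior probability that it is above 80%. Either one acts when it exceeds 0.90. For criterion 2 the action reads: "If criterion 2 > 0.90, discontinuation of inclusions with conclusion of efficacy". Criteria 3 and 4 also end in a conclusion of efficacy. They look ahead to the next 5 patients, which is a prediction horizon and not a minimum for criterion 2. An independent committee meets to "confirm the decision to continue or discontinue inclusions in the considered group based on the results of the sequential analysis".

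On size, section 6.4 says: "A total of 90 patients will be included over 12 months with 45 patients in the treatment group". Section 2.2 lists as a secondary objective "to evaluate the safety of prolonged release pasireotide".

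**The concern.** Followed as written, the efficacy rule is live from the first patient. The prior mean already sits on the 80% threshold, so a few successes are enough to push the posterior over it unless the prior is heavy. Continuous looks then give chance many opportunities to produce such a run.

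Two things are at stake. The arm could close with a conclusion of efficacy on very little evidence, sometimes when the true rate is no better than the plan's own inefficacy threshold. The trial could also end with a small fraction of the 45 planned pasireotide patients treated, and the safety objective depends on those same patients.

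**Working it through.** **The plan's own figures.** The protocol gives no operating characteristics for the stopping rules and no derivation of 45 per arm, so there is nothing to reproduce. The rules were therefore run as stated.

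**Inputs.**
- Prior mean 0.80 and Beta-binomial updating (section 6.5).
- Thresholds 60%, 80% and 0.90 (section 6.6).
- A maximum of 45 in the arm over 12 months (section 6.4).
- Assumed: prior Beta(0.8w, 0.2w) with weight w = 1, 2, 5, 10, 20.
- Criteria 1 and 2 only. The formulas of criteria 3 and 4 are not legible in the text at hand. Both lead to a conclusion of efficacy, so including them could only add efficacy stops.

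**Step 1: shortest route to criterion 2.** After n successes in n patients the posterior is Beta(0.8w + n, 0.2w). Find the smallest n for which P(rate > 0.80) exceeds 0.90. For w = 5 and n = 7 this can be done by hand: Beta(11, 1) gives 1 − 0.8^11 = 0.914.

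| Prior weight w | 1 | 2 | 5 | 10 | 20 |
|---|---|---|---|---|---|
| Straight successes needed | 3 | 4 | 7 | 9 | 13 |
| Posterior probability at that point | 0.924 | 0.907 | 0.914 | 0.901 | 0.907 |

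**Step 2: how often the rule stops.** Exact recursion over n = 1 to 45, reading criteria 1 and 2 after each patient:

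| Prior weight w | 1 | 2 | 5 | 10 | 20 |
|---|---|---|---|---|---|
| Efficacy stop by patient 20, true 80% | 59% | 50% | 29% | 20% | 10% |
| Same, looks every 5 patients | 42% | 42% | 20% | 14% | 8% |
| Efficacy stop by patient 20, true 90% | 87% | 83% | 66% | 57% | 45% |
| Efficacy concluded by patient 45, true 60% | 22% | 13% | 3% | 1% | 0.2% |

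A hand check for w = 1: three straight successes at a true 60% have probability 0.6^3 = 0.216, which is nearly all of the 22%.

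**Step 3: how many would have been treated.** The injection is "administered intramuscularly 7 to 10 days before scheduled surgery", and V5 falls between K24 and K32. The lag from injection to outcome is therefore 7 + 24 = 31 to 10 + 32 = 42 days. At 45/365 patients per day in the arm, 3.8 to 5.2 more patients are already injected when the rule is met. At the fastest stop, about 3 + 4 = 7 to 13 + 5 = 18 patients have been treated.

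**Step 4: what that means for safety, as illustration.** With no event seen, the 95% upper limit on an event rate is 1 − 0.05^(1/n): 35% at n = 7, 15% at n = 18, 6% at n = 45. The chance of seeing at least one event whose true rate is 5% (an assumed rate) is 1 − 0.95^n: 30%, 60% and 90%.

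**The case against.** The strongest reply is that the size of the problem depends on an input the protocol does not fix. The prior is still to be selected, and the SAP may specify it. With 20 pseudo-patients, an efficacy stop by patient 20 at a true 80% has probability 10%, and false efficacy at a true 60% is 0.2%. This stands. A reader might infer that the design carries a false-efficacy rate of about one in five, but that holds only at weight 1. From weight 5 upwards it is 3% or less. Early stopping is less sensitive: even at weight 20, 45% of trials stop by patient 20 if the true rate is 90%.

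A reader might also infer that an early stop would defeat the safety objective, or that safety oversight is missing. The documents support neither. Section 2.2 sets no precision or exposure target for safety, section 6.4 does not tie 45 per arm to safety, and section 3.2 regards the drug's safety as already demonstrated. Adverse events are recorded from V1 to V6 and ECGs are taken at V1 and V4. Thin safety data are therefore a consequence worth weighing, not a breach of a stated requirement.

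Finally, the stop is not automatic. The committee must confirm it, nothing in section 6.6 bars other inputs, and a charter may exist. What remains is that the only basis section 6.6 names for the confirmation is the sequential analysis of response, with no minimum number attached.

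**Conclusion.** The point holds as a cheap improvement to a rule that is stated and would perform poorly if followed as written. Criterion 2 can close the pasireotide arm for efficacy after 3 to 13 straight successes, and does so by patient 20 in 59% to 10% of trials at a true 80%. Reading the data every 5 patients softens this but does not remove it. A false conclusion of efficacy at a true 60% is material mainly at weights 1 and 2. The low number treated at the fastest stops is a secondary reason, since the protocol names no safety target.

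These figures rest on assumed prior weights with mean 80%, on criteria 1 and 2 alone, and on even accrual over 12 months.

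**What to change.** Add to section 6.6:

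> Criteria 2, 3 and 4 may close the pasireotide group only after 20 patients in that group have been observed to V5; criterion 1 applies from the start. When the committee meets to confirm a stop, it also receives the adverse events and available ECG results by arm.

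If the SAP or a committee charter already sets a minimum, a cross-reference is enough.

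Effect and cost, on the same assumptions:

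| Prior weight w | 1 | 2 | 5 | 10 | 20 |
|---|---|---|---|---|---|
| Expected pasireotide patients, true 80%: now | 20 | 25 | 33 | 37 | 41 |
| Same, with the minimum | 38 | 38 | 40 | 41 | 42 |
| Efficacy concluded, true 90%: now | 94% | 92% | 88% | 85% | 80% |
| Same, with the minimum | 87% | 86% | 85% | 83% | 79% |

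Efficacy conclusions at a true 60% fall to 0.4% or less. The price is a larger expected arm and a small loss of efficacy conclusions at a true 90%. The maximum stays at 45 per arm, and the safety tables use data already scheduled.

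The minimum does not settle safety precision. With 4 to 5 further patients already injected, closure at 20 observed means about 24 to 25 treated, for whom the zero-event upper limit is still 11% to 12%. A numerical pause rule for harm would be a separate design decision and is not needed for this repair.

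### Section 6.6 attaches an efficacy conclusion to criterion 4, which measures only precision and can be met together with the inefficacy criterion

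*Protocol*

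**What the plan says.** Protocol Section 6.6 sets four criteria, computed sequentially and separately in each group.

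- Criterion 1 is the posterior probability that the rate "is less than 60% (considered as the maximum inefficacy threshold"). Its rule is "If criterion 1 > 0.90: discontinuation of inclusions with conclusion of inefficacy".
- Criterion 2 is the posterior probability that the rate "is greater than 80% (considered as the minimum efficacy threshold"). Above 0.90 it stops the arm for efficacy.
- Criterion 3 uses the predictive distribution of responses in the next five patients. Above 0.90 it also stops for efficacy.
- Criterion 4 is described this way: "The fourth discontinuation criterion will be based on the maximum expected gain in terms of the width of the 95% credibility interval". It looks five patients ahead. Its rule is "If criterion 4 < 0.05: discontinuation of inclusions with conclusion of efficacy".

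An independent committee confirms whether inclusions continue or stop. Section 6.5 sets a Beta prior for each arm, with "density focused on the anticipated response rate of 80% in the group receiving treatment and 60% in the treatment-free group". Section 6.4 plans the size: "A total of 90 patients will be included over 12 months with 45 patients in the treatment group", and the same number in the control arm.

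**The concern.** Criteria 1 and 2 compare the response rate with a threshold. Criterion 4 compares nothing with a threshold rate. It asks whether five more patients would narrow the interval appreciably. A small gain means the estimate is settling, whether at 40%, 60% or 85%. The most it can justify is stopping because further precision is not worth the patients.

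With an efficacy conclusion attached, an arm can be reported as successful because it has been observed for long enough. The rules apply to each group, so this includes the placebo arm. Criterion 1 is the only route to inefficacy, and nothing says which conclusion stands when criteria 1 and 4 are both met. Section 3.1.1 wants the control arm to establish the incidence of lymphocele and to help size a phase III trial, so both the label and the stopping point matter.

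**Working it through.** **Plan's own figure.** There is none to reproduce. Section 6.4 holds that 45 per arm needs no justification in a Bayesian study, and the protocol gives no operating characteristics for these rules.

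**Inputs from the protocol.** Thresholds 0.60 and 0.80; cut-offs 0.90 and 0.05; look-ahead of 5; posterior Beta(a+r, b+n−r) after r responses in n patients; prior centred on 0.80 (treatment) or 0.60 (control); maximum n = 45.

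**Assumptions.** The values of a and b are not given, so prior weights a+b of 1, 2, 5 and 10 and a uniform prior Beta(1,1) were tried. The criterion 4 expression is not readable, so the verbal definition was used. With W the width of the equal-tailed 95% interval:

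C4 = max over s = 0..5 of [W(a+r, b+n−r) − W(a+r+s, b+n−r+5−s)].

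The criterion 3 expression is not readable either, so it was left out of the main runs. There was one look per evaluated patient, with criterion 1 checked first, then 2, then 4.

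**Step 1: two data sets, uniform prior.**

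- 10/20, posterior Beta(11,11): P(rate<60%) = 0.83 and P(rate>80%) = 0.001. W = 0.4044, falling to 0.3608 if the next five are all failures or all responses. C4 = 0.0436 < 0.05, so the written conclusion is efficacy.
- 10/22, posterior Beta(11,13): P(rate<60%) = 0.919 > 0.90, so the conclusion is inefficacy. W = 0.3869, falling to 0.3443 if the next five all fail. C4 = 0.0426 < 0.05, so the conclusion is also efficacy. P(rate>80%) = 0.0001.

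**Step 2: timing and conclusions at a true rate of 60%**, by exact recursion over all response paths to n = 45. The columns C4, C2 and C1 give the percentage of arms stopped first by that criterion.

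| Prior | Last n with C4 ≥ 0.05 possible | C4 | C2 | C1 | Mean evaluated n, with / without C4 |
|---|---|---|---|---|---|
| Beta(0.8,0.2) | 22 | 55 | 22 | 23 | 14.7 / 26.3 |
| Beta(1.6,0.4) | 21 | 69 | 13 | 18 | 16.8 / 32.1 |
| Beta(4,1) | 18 | 91 | 3 | 6 | 17.4 / 40.3 |
| Beta(8,2) | 13 | 99 | 1 | 0.2 | 13.6 / 43.7 |
| Beta(1,1) | 21 | 61 | 1 | 38 | 15.0 / 28.6 |

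Adding one to the second column gives the patient by which C4 must have fired: 23, 22, 19, 14 and 22. For the placebo arm (prior centred on 0.60, true rate 60%), C4 gives efficacy in 58% (weight 1) to 91% (weight 10).

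**Step 3: lower true rates.** For the same priors in the same order:

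- At 50%, criterion 1 stops first in 50%, 44%, 21%, 1% and 65%.
- At 40%, it stops first in 78%, 74%, 47%, 5% and 87%.

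**Step 4: other readings of the gain.**

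- Predictive mean instead of maximum: C4 fires by patient 18 or earlier for every prior tried.
- Unsigned change in width: firing is no longer guaranteed at counts near 0% or 100%, but the results at observed rates of 40% to 80% do not change.
- Gain relative to current width: at 10/22 it is 0.0426/0.3869 = 0.11, which does not fire. At a true 60%, C4 decides 0%, 0%, 0%, 1.5% and 0% of arms, and 49% to 92% of arms reach 45 without a stop.

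**The case against.** The strongest reply is that the timing rests on a formula nobody can read here. A reader might infer that criterion 4 is bound to fire near patient 23 whatever the data, that 45 per arm is therefore never reached, and that an ineffective drug is bound to be declared effective. The protocol does not support that. A relative gain is compatible with the surviving words and makes criterion 4 almost inactive, although a difference in width is arguably the more natural reading. The 10/22 overlap is also computed on the difference reading.

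Other replies stand in part.

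- Not every false efficacy conclusion comes from criterion 4. At weights 1 and 2, criterion 2 contributes 22 and 13 points of the combined 77% and 82%.
- Criterion 1 often stops first when the true rate is 50% or lower and the prior is weak.
- With a look after every patient, criteria 1 and 4 seldom become true at the same look. In the 10/22 example, criterion 4 would already have been met at patient 21. The conflict then arises when outcomes mature after a stop or the committee continues. Even accrual of 45/12 = 3.75 per arm per month and 35 to 38 days from injection to outcome leave 4 to 5 patients pending (3.75 × 35/30.4 = 4.3; 3.75 × 38/30.4 = 4.7).
- The committee must confirm a stop, so stopping is not automatic. But its stated task is to confirm continuing or stopping inclusions, and nothing has it revise the conclusion attached to the rule.

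A statistical analysis plan, not available here, might define the formula. The point concerns a conclusion that the protocol states, not a detail it leaves out.

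**Conclusion.** The rule is wrong as written. An interval-width measure cannot carry an efficacy conclusion, and this follows from Section 6.6's own definition under any reading of the formula or prior. The absence of a precedence between criteria 1 and 4 is a second, smaller defect.

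The size is conditional. If the gain is a plain difference in width, criterion 4 acts at about half of the planned 45 or sooner. For a drug no better than the anticipated control rate, it is then the most frequent stopping reason under every prior run through the recursion. If the gain is relative, the wrong label seldom comes into play before 45. Claims that the rule always fires, or that an ineffective drug is always declared effective, go further than the text allows.

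**What to change.** In Section 6.6, replace the conclusion attached to criterion 4 with: *estimate judged sufficiently precise; no efficacy conclusion*. Alternatively, drop criterion 4 as a decision rule. State that an efficacy conclusion may rest only on criteria 2 and 3, and that criterion 1 prevails when it and criterion 4 are both met. Changing the look-ahead from five patients to all those remaining would be optional redesign and is not needed.

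The relabelling is an edit to one line plus a precedence sentence. The cost is fewer early efficacy stops. If criterion 4 is dropped, mean evaluated patients per arm at a true 60% rise from about 14–17 to 26–44 (weights 1 to 10), within the planned 45.

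False efficacy conclusions do not vanish. At a true 60%, criterion 2 still gives about 22%, 13%, 3% and 1% (weights 1, 2, 5, 10) and 1% (uniform prior). If criterion 3 is assumed to be the predictive probability of at least four responses in the next five, criteria 2 and 3 together give 36%, 22%, 5%, 1% and 1%.
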